### Analysis

2.10

Analyses will be descriptive and exploratory, consistent with the pragmatic, non-randomized design and primary focus on implementation outcomes. Acceptability, adoption, feasibility, fidelity, penetration, and short-term sustainability will be summarized at the facility level using appropriate summary statistics. Results will be reported individually by facility and stratified by facility type (district vs. referral hospital) to characterize variation in implementation experience across site types.

Acceptability will be assessed through a simple summary statistics including means, and ranges of scores from providers surveys, and through a quantifying data found in provider and hospital superintendent surveys.

Adoption will be assessed through a narrative description of how workflows were deployed across facilities using data from provider surveys, REDCap clinical records, and facility clinical records.

Feasibility will be assessed quantitively through the percentage of workflows that are completed using data from REDCap clinical records and qualitatively through barriers reported in the provider structured surveys and monthly monitoring reports.

Fidelity will be quantified using adherence metrics including completeness of RedCap registry forms, echocardiographic protocol compliance, and documented protocol deviations from monthly monitoring reports.

Short-term sustainability will be evaluated quantitatively based on continued case enrollment, REDCap registry use, and participation in quality assurance processes at 12 months using data from REDCap activity logs and monthly reports.

Exploratory care-process indicators will be summarized at the patient level, including diagnostic patterns, concordance with central review, timeliness of diagnosis, and follow-up completion. In cases where initial diagnosis is unclear and reclassification occurs, final diagnoses will be used where possible. These measures are descriptive and not intended to assess clinical effectiveness. The study is not designed for formal between-facility comparisons. Patient-level registry data, provider-level survey data, and facility-level monitoring reports serve complementary descriptive roles and are not formally integrated through multilevel modeling, consistent with the pragmatic, single-arm design.

As this is an early-phase descriptive study, no *a priori* thresholds for successful implementation are defined; outcomes will be interpreted descriptively and in light of contextual factors identified through CFIR domains.

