### Objectives

1.1

The primary objective of the study described in this protocol is to assess the acceptability, feasibility and facility-level adoption of the described ARF case-finding and registry program embedded within routine district and referral hospital care across diverse geographic settings in Nepal. This study does not evaluate the clinical effectiveness of ARF case-finding or its impact on RHD outcomes, which are beyond the scope of this early implementation evaluation.

Secondary objectives are: to measure fidelity to standard operating procedures (SOPs), defined as adherence to ARF diagnostic criteria, echocardiographic protocols, and registry documentation requirements; to describe the penetration of ARF case-finding within participating facility catchment areas; to evaluate short-term sustainability, defined as continued program operation and sustained workflow adherence at 12 months; to identify contextual factors associated with variation in adoption and fidelity across KIOCH and referral facilities using selected Consolidated Framework for Implementation Research (CFIR) domains.

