#### ARF diagnostic criteria

2.6.3

The 2015 modified Jones criteria (13) for high-risk populations will be used. The diagnosis of ARF is made if two major or one major and two minor criteria are met along with the evidence of streptococcal infection. If ARF is thought to be a recurrent episode, three minor criteria can be used to make the diagnosis. Major criteria include presence of carditis, mono- or polyarthritis, polyarthralgia, chorea, erythema marginatum, and subcutaneous nodules. Minor criteria include monoarthralgia, fever ≥38.0 °C, elevated inflammatory markers: ESR ≥30 mm/h and/or CRP ≥3.0 mg/dL, or prolonged PR interval on ECG. Prolonged PR interval is counted as a minor criterion only if carditis is not being used as a major criterion. There must be evidence of preceding group A streptococcal infection which is required for all except isolated chorea or indolent carditis. Antistreptolysin O Titer (ASOT) testing is provided to all facilities by the PRIMA study and will be the most common GAS antibody test used, though anti-DNase B titer, positive throat culture for GAS, and positive rapid antigen detection testing for GAS can also be used.

Carditis may be clinical or subclinical. Subclinical carditis is defined by Doppler echocardiographic evidence of pathological mitral or aortic regurgitation and morphologic changes as detailed in the 2023 World Heart Federation guidelines for the echocardiographic diagnosis of RHD (14). Echocardiographic assessments are performed using standardized imaging checklists which specifically include the criteria for pathological regurgitation and morphologic change. Echocardiograms are all uploaded for central review by cardiologists to support diagnostic consistency and fidelity. Kathmandu-based cardiologists serve as the final interpretive authority for echocardiographic findings, consistent with specialist referral practice within Nepal's health system. All clinics are equipped with a cardiac ultrasound machine.

Cases in which diagnostic criteria are not clearly met are reviewed by a study cardiologist, and children may be classified as suspected or probable ARF when appropriate. Diagnostic classification may be updated over time as additional clinical, laboratory, or echocardiographic information becomes available during follow-up, which reflects real-world practice.

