Feasibility	Facility/provider	Can the standardized workflow be delivered within routine inpatient and outpatient care?	Reported workflow barriers Time burden estimates Documentation of contextual constraints	Monthly monitoring reports Provider structured surveys
Fidelity	Facility/provider	Are ARF diagnostic and registry procedures implemented according to centrally defined SOPs?	Proportion of evaluations meeting Jones criteria documentation standards Echocardiography completeness and image adequacy Registry completeness Frequency and nature of protocol deviations	REDCap clinical data Monthly monitoring reports
Sustainability	Facility	Is the program still operational with sustained adherence at 12 months?	Continued ARF case enrollment activity Continued registry use Ongoing participation in QA processes Sustained workflow adherence	REDCap clinical data Monthly monitoring reports
—	Patient/Facility	How is the standardized workflow functioning clinically during early implementation?	Number and proportion of ARF diagnoses among evaluated children Diagnostic concordance with central cardiologist review Time from symptom onset to diagnosis Time from diagnosis to initiation of prophylaxis Follow-up completion at 3, 6, and 12 months	REDCap clinical data Facility clinical records

Exploratory care-process indicators will be assessed at the patient level and are intended to characterize whether the intervention may function to improve ARF care in the absence of pre-implementation comparator data. These include the number and proportion of ARF diagnoses among evaluated children, accuracy and timeliness of diagnosis, linkage to follow-up care, and follow-up completion over time. These measures are descriptive and are not intended to evaluate long-term clinical effectiveness.

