#### Data sources

2.9.1

Data sources include facility clinical records, REDCap clinical data, provider and hospital superintendent surveys, and monthly monitoring reports with site-based study leads.

Facility clinical records: We will examine the routine paper-based clinical forms that exist in the facilities. We will examine background data on participants, as well as monthly records for participants who are positive for ARF. At the end of the program, researchers will hand search clinical forms to extract relevant data.

REDCap clinical data: Three types of REDCap clinical data will be used for this study.
When a suspected case is referred to a participating facility, the study encounter and suspected diagnosis will be recorded in REDCap.If the case screens positive for ARF, their echocardiogram will be reviewed by a Kathmandu-based cardiologist who will report their echocardiographic findings in REDCap.Per study protocol, at three study points (3, 6, and 12 months) patients diagnosed with ARF will be monitored for progress. These visits will be conducted using REDCap forms.Provider surveys: Surveys will be distributed at 12 months to all providers (one doctor and one nurse at each facility). Surveys will consist of a mix of multiple choice, Likert-scale and free text questions. These will be conducted in a mix of English and Nepali and will be conducted through Google forms.

Hospital superintendent surveys: Surveys will be distributed at 12 months to the superintendent in charge of each facility enrolled in this study. Surveys will consist of a mix of multiple choice, Likert-scale and free text questions. These will be conducted in a mix of English and Nepali and will be conducted through Google forms.

Monthly monitoring reports: Once a month, a central researcher from KIOCH will hold a “monthly check-in” with each of the 11 site-based study leads. These free-form discussions will cover barriers and solutions encountered over the past month, as well as number of cases, perceptions of case mix, and any questions that have arisen. These check-ins will not have audio recording but the KIOCH researcher will take detailed notes.

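### Registry documentation fidelity is measured by completeness of REDCap forms, which on its natural reading does not fall when a child due for entry is never entered

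*Protocol article*

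**What the plan says.** All references are to the protocol article.

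- **Objectives (1.1).** Fidelity to the standard operating procedures is a secondary objective, "defined as adherence to ARF diagnostic criteria, echocardiographic protocols, and registry documentation requirements". Identifying contextual factors associated with variation in adoption and fidelity is another.
- **Data sources (2.9.1).** One documentation requirement is stated outright: "When a suspected case is referred to a participating facility, the study encounter and suspected diagnosis will be recorded in REDCap". Clinical evaluation workflow (2.6.2) gives a narrower rule, under which cases judged likely to be ARF go into the registry.
- **Table 1 (2.8), Fidelity row.** The data elements include "Proportion of evaluations meeting Jones criteria documentation standards" and "Registry completeness", neither with a stated denominator. The sources are REDCap clinical data and monthly monitoring reports. Facility clinical records are listed for Penetration, Adoption and the exploratory indicators, but not for Fidelity.
- **Analysis (2.10).** The metric is stated as: "Fidelity will be quantified using adherence metrics including completeness of RedCap registry forms, echocardiographic protocol compliance, and documented protocol deviations from monthly monitoring reports". Results are shown facility by facility and by facility type. Formal comparison between facilities is disclaimed, and no thresholds for success are set.
- **Ethical considerations (2.11).** Families who decline are cared for outside the registry.

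**The concern.** Leaving a child out of the registry is the most direct way to fail a documentation requirement. A completeness percentage calculated over entered forms cannot register that failure, because the missing child is in neither the numerator nor the denominator. A facility short of time that enters only its straightforward cases can therefore look more faithful than one that enters every child and leaves some fields blank.

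What is at stake is the secondary objective on variation in fidelity. Table 2 assigns determinant data to explaining that variation. The Discussion expects staff turnover and high patient volume to affect fidelity, and under such pressures entries may be skipped. If the fidelity figure is insensitive to skipped entries, the contextual explanation is fitted to the wrong pattern.

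**Working it through.** The plan gives no figure to reproduce. The check has three parts: whether any planned measure would show non-entry, how far the metric can mislead, and whether the denominator of a better metric is defined.

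**1. Where could non-entry show?**

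- *Form completeness (2.10).* It has a value only for a form that has been opened, so non-entry does not show.
- *Table 1 elements.* "Registry completeness" could be read to cover capture of cases. But REDCap cannot count children missing from REDCap, and the row's only other source is the monthly reports.
- *Protocol deviations.* Section 2.6.2 requires deviations from the procedures to be documented and reviewed monthly, and 2.10 counts them under fidelity. Section 2.9.1 describes the monthly check-ins as free-form, unrecorded conversations with the site lead, documented in notes. Non-entry shows here only if the site reports itself.
- *Penetration count.* Table 1 counts children evaluated per site from REDCap and facility clinical records, so a shortfall could be visible. No analysis sets that count against registry entries, and 2.9.1 describes the record review as covering participants.

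Non-entry is therefore weakly and indirectly visible, and not visible in the form-completeness metric itself.

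**2. Size, with assumed figures (none is in the documents).**

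Let D be the children due for entry, E the children entered, and f the completeness of the entered forms.

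- Capture = E / D
- Due documentation delivered = (E / D) × f

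This product is used only for the illustration; the plan has no composite score.

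| Facility (D = 60) | E | f | Capture | Delivered |
|---|---|---|---|---|
| A, selective | 20 | 100% | 20/60 = 33% | 0.333 × 1.00 = 33% |
| A, less selective | 40 | 100% | 40/60 = 67% | 0.667 × 1.00 = 67% |
| B, full entry | 60 | 90% | 60/60 = 100% | 1.00 × 0.90 = 90% |

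On form completeness A stands above B in both versions. On documentation delivered it stands below.

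A second set of assumptions counts complete forms instead of filled fields, with D = 40. The full-entry facility completes 32 of 40 forms, which is 80.0% on either denominator.

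| Selective facility | Complete / entered | Complete / due |
|---|---|---|
| 20 entered | 19/20 = 95.0% | 19/40 = 47.5% |
| 30 entered | 27/30 = 90.0% | 27/40 = 67.5% |
| 36 entered | 31/36 = 86.1% | 31/40 = 77.5% |

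The order reverses in each row. At 95% form completeness, a facility falls below the 80% full-entry facility once it enters fewer than 0.80 / 0.95 = 84.2% of due children.

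**3. Is the denominator defined?**

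Not yet. Suppose a facility sees 60 referred suspected cases, judges 20 likely to be ARF, and enters those 20. Under 2.6.2 its capture is 20/20 = 100%; under 2.9.1 it is 20/60 = 33%. The same conduct is full adherence under one section and poor adherence under the other. The gap in the form-completeness metric exists under either rule, but a capture ratio has no fixed meaning until there is one rule.

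**The case against.** The strongest reply has four parts.

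*The article does not say that only existing forms count.* The list in 2.10 is introduced as non-exhaustive, Table 1 leaves denominators open, and a condensed article may leave them to a fuller document. This stands in part: the reading is natural but not explicit. What goes beyond missing detail is that the Fidelity row names its sources and leaves out facility records, the one listed source that could reveal unentered children.

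*Non-entry is not free of consequence.* A reader might infer that skipping the registry costs a facility nothing. The documents do not support that, because deviations are themselves a fidelity metric and the Penetration count may show a shortfall. The supportable statement is narrower: it costs nothing on form completeness, and the other two routes are weak.

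*No facility is ranked.* A reader might infer that the plan would place a selective facility above a thorough one. It contains no ranking, composite or threshold, and it disclaims formal comparison. This stands. Results are still shown by facility, and variation in fidelity is to be described and explained, so a misleading order can be read off the results.

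*Not every evaluated child outside the registry is a failure.* This stands. Section 2.6.2 enters likely ARF only, and 2.11 keeps families who decline outside the registry. Counting all evaluated children as due would silently adopt 2.9.1 over 2.6.2.

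**Conclusion.** The concern holds in a limited form. Fidelity is defined to include the registry's documentation requirements, but the stated metric and sources measure how well entered children are documented, not whether children due for entry were entered. Selective entry can therefore make a facility appear more faithful than one that enters everyone.

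The direction follows from the arithmetic. The size cannot be taken from the documents: in the assumed examples, form completeness of 86% to 100% goes with 33% to 77.5% of due documentation. These figures show what is possible, not what is likely. The conclusion rests on reading form completeness as calculated over entered forms. It affects the description of a secondary objective. The primary outcomes are acceptability, feasibility and adoption, and no formal test is involved. The change is worth making because it is small and a count of evaluated children is already planned.

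**What to change.** 1. **Settle the entry rule.** Reconcile 2.6.2 with 2.9.1 so that one statement says which children must have a REDCap encounter record.
2. **Add registry capture to 2.10 and the Fidelity row.** By facility: children with a REDCap encounter record, divided by children meeting the entry rule less those who declined. Build the denominator on the count of evaluated children already planned under Penetration, and list facility clinical records as a Fidelity source. Extend the end-of-program hand search so that it yields an aggregate count of evaluated children, not only data on participants. No individual data on children outside the registry are needed. If the full protocol has no tally of refusals, one is required.
3. **Report capture and form completeness side by side.** Do not present form completeness alone as documentation fidelity.

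Use of ASOT tests may serve as a rough cross-check, since "Antistreptolysin O Titer (ASOT) testing is provided to all facilities by the PRIMA study"; one child may have more than one test, and some may be for PRIMA controls. Tricefy uploads should not serve, because 2.7 links them by study ID and they would probably miss the same unentered children.

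The cost is somewhat more record review. The denominator drawn from paper records is approximate and should be labelled so.

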### Ethical considerations

2.11

The study was approved on December 1, 2025, by the Nepal Health Research Council. Written informed consent will be obtained from parents or guardians, and assent from children aged 12 years or older for permission to participate in the PRIMA research study and for registry enrollment. Parents and children who do not wish to participate in the study will continue to receive routine care as medically indicated without inclusion in the registry.

## Discussion

3

This protocol describes the implementation of a standardized ARF case-finding and registry program embedded within routine district- and referral-level care across 11 facilities in Nepal. The primary aim is to evaluate early implementation outcomes and explore contextual factors influencing implementation. In a setting where ARF is frequently under-recognized and follow-up fragmented, establishing a consistent operational workflow represents a necessary first step toward earlier detection.

Despite a high prevalence of RHD, Nepal lacks a coordinated system for early identification of suspected ARF and registry-based tracking of follow-up and secondary prophylaxis. By integrating ARF evaluation into district-level services aligned with PEN-Plus infrastructure, this program aims to strengthen routine clinical capacity rather than introduce stand-alone screening programs that may be difficult to sustain. Earlier identification of ARF may enable timely initiation of secondary prophylaxis, which reduces progression to valvular heart disease. The emphasis on centralized training, clearly defined SOPs, and ongoing quality assurance reflects a deliberate focus on fidelity and reproducibility during early implementation. Over time, this infrastructure may also enable more consistent monitoring of disease progression and outcomes and, if successful, may inform future national scale-up.

Several challenges are anticipated. Diagnosis of acute rheumatic fever remains clinically complex, particularly in high-burden settings where presentations may be heterogeneous and overlapping infectious etiologies are common. Although the 2015 modified Jones criteria provide standardized guidance, diagnosis relies on combinations of clinical findings, laboratory evidence, and echocardiographic interpretation that may be incomplete or evolving at initial presentation. Consequently, some children may initially be classified as indeterminate or probable ARF, with diagnostic status evolving as additional clinical information becomes available. Staff turnover, variation in infrastructure, and high patient volume across participating facilities may further influence adoption and fidelity of the standardized workflow. Geographic barriers and socioeconomic constraints may affect retention in follow-up independent of program performance. For these reasons, this study prioritizes documentation of contextual factors and structured assessment of workflow adherence during the first 12 months of implementation.

Additionally, the symptom-triggered case-finding approach used in this program will not identify children with subclinical carditis detectable only by echocardiography in the absence of clinical symptoms. Population-based echocardiographic screening would be required to capture this group; however, such programs are resource-intensive and not feasible for routine implementation within most health systems in low-resource settings. The purpose of this program—and of this implementation study—is to evaluate whether structured ARF case-finding and follow-up can be pragmatically embedded within existing district-level health system infrastructure, rather than to conduct population-level RHD surveillance.

Although this protocol does not evaluate long-term clinical effectiveness, the implementation data generated will inform future analyses examining diagnostic patterns, barriers and facilitators to program delivery, and additional Proctor outcomes such as cost. If feasible and sustainable within the Nepalese health system, this approach may offer a pragmatic model for other RHD-endemic low- and middle-income countries seeking to embed ARF detection within decentralized care platforms where high disease burden, limited specialist availability, and fragmented follow-up remain common challenges.

